## Abstract

**Background:**

Musculoskeletal conditions account for 16% of global disability, resulting in a negative effect on millions of patients and an increasing burden on health care utilization. Digital technologies that improve health care outcomes and efficiency are considered a priority; however, innovations are often inadequately developed and poorly adopted. Further, they are rarely tested with sufficient rigor in clinical trials—the gold standard for clinical proof of efficacy. We have developed a new musculoskeletal Digital Assessment Routing Tool (DART) that allows users to self-assess and be directed to the right care. DART requires usability testing in preparation for clinical trials.

**Objective:**

This study will use the iterative convergent mixed methods design to assess and mitigate all serious usability issues to optimize user experience and adoption. Using this methodology, we will provide justifiable confidence to progress to full-scale randomized controlled trials when DART is integrated into clinical management pathways. This study protocol will provide a blueprint for future usability studies of mobile health solutions.

**Methods:**

We will collect qualitative and quantitative data from 20-30 participants aged 18 years and older for 4 months. The exact number of participants recruited will be dependent on the number of iterative cycles required to reach the study end points. Building on previous internal testing and stakeholder involvement, quantitative data collection is defined by the constructs within the ISO 9241-210-2019 standard and the system usability scale, providing a usability score for DART. Guided by the participant responses to quantitative questioning, the researcher will focus the qualitative data collection on specific usability problems. These will then be graded to provide the rationale for further DART system improvements throughout the iterative cycles.

**Results:**

This study received approval from the Queen Mary University of London Ethics of Research Committee (QMREC2018/48/048) on June 4, 2020. At manuscript submission, study recruitment was on-going, with data collection to be completed and results published in 2021.

**Conclusions:**

This study will provide evidence concerning mobile health DART system usability and acceptance determining system improvements required to support user adoption and minimize suboptimal system usability as a potential confounder within subsequent noninferiority clinical trials. Success should produce a safe effective system with excellent usability, facilitating quicker and easier patient access to appropriate care while reducing the burden on primary and secondary care musculoskeletal services. This deliberately rigorous approach to mobile health innovation could be used as a guide for other developers of similar apps.

**International Registered Report Identifier (IRRID):**

DERR1-10.2196/27205

## Introduction

### Background

Musculoskeletal conditions are recognized as a global issue, with between 20%-33% of people living with a painful musculoskeletal condition. These conditions are the highest contributor to global disability at 16%, resulting in a negative effect on millions of patients and an increasing burden on health care utilization [1]. Musculoskeletal conditions are prevalent throughout the lifespan and are associated with early work retirement and reduced ability to participate socially [2]. In developed countries, they present the most significant proportion of lost productivity in the workplace, leading to a significant impact on the gross domestic product and health care costs [3-6]. Musculoskeletal conditions can affect as many as 1 in 4 adults and are set to continue rising, being associated with increased life expectancy and reduced activity [4,5]. Access to the “right person, right place, first time” is considered a key factor in improving musculoskeletal condition outcomes and in reducing unwarranted variations in clinical pathways, such as unnecessary secondary care consultations and investigations [7]. Musculoskeletal triage as a single point of access is effective across various outcome measures, including user satisfaction, diagnostic agreement, appropriateness of referral, and reduction in patient waiting times [8]. Importantly, triage has also shown a reduction in cost across the musculoskeletal pathway, which is particularly crucial in overburdened health care systems, where triage can be performed effectively via several methods and by a range of clinicians [9-11]. For example, the National Health Service England is introducing physiotherapists as musculoskeletal first-contact practitioners; however, this is dependent on the recruitment of a significant number of clinicians with the associated challenges [7]. Mobile health (mHealth) technology is proposed as a cost-effective solution for improving health care delivery [12,13]. Although many mHealth tools have not demonstrated cost-effectiveness or have shown merely to shift spending to another part of the health system [14], it would seem logical that a digital alternative to physio-led triage, able to replicate the same stratification of care and reduction in costs, is a desirable objective. Thus, Optima Health has developed the Digital Assessment Routing Tool (DART) mHealth system to assess the patient’s musculoskeletal presentation through a series of questions and responses accessed via their mobile devices. The patient is taken through a subjective assessment, which is driven by 9 sets of clinical algorithms that cover all body regions, similar to a clinician performing a virtual triage by telephone or videocall. At the end of the assessment, the patient is given a signposting recommendation to one of the clinical services available to them within the musculoskeletal pathway. The objective is to provide patients with easily accessible, safe, and effective access to musculoskeletal services, while releasing valuable clinical resources to consistently work at the top of their skill set, where they add the greatest value to the patient journey. The development of more remote health care delivery options has been greatly accelerated by the COVID-19 pandemic and the benefits offered by a virtual approach are likely to support further uptake of systems such as DART. Patients are already making their own decisions about accessing health care for a range of conditions or increasingly turning to unvalidated self-help apps for advice that can be unhelpful or even potentially harmful [15,16]. Guidance for safe and effective development of mHealth apps has been published by several national and international organizations [17-20]. While these recommendations provide advice for developers, it is recognized that there remains no single regulatory framework to which all mHealth developments must conform [21] and that work remains to develop a suitable legal framework [22].

Up to 2017, there was an exponential increase in the rate of mHealth app releases, resulting in over 259,000 apps available in just the major app stores alone [23,24]. However, many mHealth apps have subsequently fallen, with many unsuccessful attempts to scale up from a prototype to successful implementation. Inattention to usability during the design and testing phases has been cited as the potential cause [25-27], contributing to the high abandonment rate [28]. Usability is crucial in the development of mHealth systems and is reflected within guidance documents relating to standards for design, development, testing, and implementation of these devices [17-19]. Usability has been defined as the extent to which a system can be used by specified users to achieve specified goals with effectiveness, efficiency, and satisfaction in a specified context of use [19]. These constructs will all be assessed during the study (Figure 1). However, there is little agreement about the most effective methodology for usability testing, with researchers using a combination of different design components to assess mHealth apps [29]. The iterative convergent mixed methods design used for this research will provide a more holistic assessment of DART compared with other mHealth studies. Although quantitative questionnaires are the most frequently used method for assessing mHealth system usability [29], they are unlikely to identify the specific problems that need to be addressed. Questionnaire scores only give a general overview of usability, without providing the level of understanding of usability problems required for system iteration. Qualitative studies alone are not able to provide a definitive level of acceptability of a system. Iteration is recognized as a key enabler of successful products but is not included by most developers, where the usability testing of a final version is often immediately prior to deployment [29]. The inclusion of patient and public involvement during mHealth testing allows users to bring their own personal perspectives into the process, giving researchers the understanding of usability issues that would not have otherwise been recognized [30]. This study will combine all these elements into a methodology specifically developed to assess an mHealth triage or symptom checker. The iterative approach of cyclical evaluation and improvement plus mixed methods allows richness while quantifying use, thus maximizing usability and system adoption.

**Figure 1 figure1:**
[figure not shown]
ISO 9241-210:2019 constructs and definitions and examples of digital assessment routing tool context of use. DART: Digital Assessment Routing Tool; mHealth: mobile health.

### DART Overview

DART is a first-contact mHealth system utilizing 9 musculoskeletal clinical algorithms, configured to provide the patient with a recommendation to the correct intervention level (Figure 2). Designed specifically for managing musculoskeletal conditions, it delivers a narrower but deeper assessment than that found with more generic symptom checkers. The patient can self-assess using a computer, tablet, or smartphone. Alternatively, the content can be delivered by a remotely situated clinician or a nonclinical administrator by telephone or videocall. The patient selects the body region related to his/her primary problem and is then presented with a varying number of questions, depending on the nature of his/her symptoms and previous responses. Serious pathology is identified and signposted at the start of the assessment, with less urgent medical referrals being identified as the patient passes down the questioning. Algorithms are configured to match the provider’s clinical services based on evidence-based practice and sector-specific referral criteria. DART can be applied across any number of health care systems, including public and private services. DART typically signposts to emergency or routine medical assessment, specific condition specialists, physiotherapy, self-management programs, or psychological support services. Referral thresholds can be configured to match service requirements, such as increasing the volume of patients directed to self-management or physiotherapy. Situated next to the questions are information boxes, which assist the patient in answering the question, thereby improving the accuracy of the responses. DART has an integral reporting function, thereby allowing the analysis of individual and amalgamated patient data to assess the system and clinical pathway performance.

**Figure 2 figure2:**
[figure not shown]
Digital Assessment Routing Tool mobile health system.

### Previous Work

This usability study is part of a larger project, bringing DART from concept to implementation through a series of clinical and academic research work packages. To assess algorithm clinical validity, 2 reports were commissioned by Optima Health and undertaken by a panel of 5 consultant clinicians prominent in the musculoskeletal field. The first round of desktop evaluation consisted of experts inputting symptoms from 98 clinical scenarios (including red flags and complex presentations) into DART. The DART recommendation was assessed by the expert as being correct, arguably correct, or disagree. Feedback from the experts was incorporated into a new iteration, leading to improved DART accuracy during the second panel review. Based on their opinions, the panel recommended that the clinical validity was sufficient to allow DART to proceed to further research studies. The initial usability study protocol went through a series of iterations within an internal review process, comprising the research project team and DART system developers to arrive at the final version presented in this paper. Using a new usability testing methodology, this study will provide a rich understanding of how users interact with DART and guide further iterations. The impact of this will be to optimize usability before evaluating the safety and effectiveness of DART in a randomized controlled trial.

### Research Aim, Objectives, and End Points

The aim of this study is to assess and optimize DART usability, which could result in maximizing user adoption. The objectives are as follows: (1) to understand what users consider to be strengths and weakness of using DART, (2) to identify usability issues and map to a usability problem grade to inform the next DART iteration development, and (3) to complete a cycle of iterations until usability reaches a predefined acceptable level. The end points are as follows: (1) all Grade 1 and 2 usability problems have been mitigated following a minimum of 3 user group sessions and (2) system usability scale score is 80 or greater after a minimum of 3 user group sessions plus 1 additional session, representing a “good” or better system.

## Methods

### Study Design

This study will use an iterative convergent mixed methods design, as described by Alwashmi et al [31]. The collection and integration of quantitative and qualitative data of direct relevance to the DART mHealth app will be used to inform subsequent DART usability improvements (Figure 3). The first phase of data collection will consist of 5 interviews with individual participants who have used the tool to identify key usability issues and gain a baseline system usability scale score. It has been suggested that 5 participants are likely to expose about 80% of the usability issues [32]. Although it is recognized that the DART target population will be heterogenous, the first round of interviews is expected to expose key issues from the sample. This will be followed by group sessions to capture a greater diversity of potential DART user population to improve validity of the data. Owing to logistic requirements, interview sessions will be conducted remotely using Microsoft Teams videoconferencing software and web-based questionnaires.

**Figure 3 figure3:**
[figure not shown]
Digital Assessment Routing Tool usability study iterative convergent mixed methods design. DART: Digital Assessment Routing Tool; SUS: system usability scale.

### Participant Recruitment

A stratified purposive sampling method will be used to gather information from participants able to access the internet as well as to explore the scope of potential DART accessibility [33]. We will use a criterion-based selection, categorizing participant characteristics of age, internet use, sex, English for Speakers of Other Languages groups—all of which are subgroups that have shown to contribute small differences in internet use [34]. To ensure that participants are included from groups potentially less likely or able to use mHealth systems, a sampling matrix will be used, which provides quotas specifying the number of people required for each characteristic [33]. Recruitment of 20-30 participants will be via convenience sampling and snowballing; study recruitment will continue until there is a representative sample from each category defined by the sample matrix and the study end points being reached. Recruitment material will be distributed to local community groups, Optima Health’s existing client base of employers and their staff, plus Queen Mary University of London (QMUL) students. Potential participants expressing an interest will be sent a patient information sheet and consent form (Multimedia Appendix 1). They will have an opportunity to review this material and if they wish to proceed, they will be registered for the study.

### Inclusion Criteria

The study participant inclusion criteria are as follows: (1) adults older than 18 years; (2) able to speak and read English; (3) live in the United Kingdom; (4) access the internet at least once every 3 months; (5) has access to a smartphone, tablet, or laptop; and (6) current or previous experience of a musculoskeletal condition.

### Exclusion Criteria

The study participant exclusion criteria are as follows: (1) significant visual or memory impairment sufficient to affect the ability to answer questions and recall information in an individual or group discussion setting; (2) medically trained, musculoskeletal health care professional, for example, doctor, physiotherapist; (3) relatives or friends of the researchers; and (4) Optima Health employees.

### Study Duration

It is anticipated that this study will last for up to 3 months after receiving the ethical approval. However, this will be dependent on the number of DART iterations required to achieve the end points. Participants who have raised high-grade usability problems will be invited to participate in a subsequent study session to assess the impact of DART system changes.

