### Data Collection

Following consent being given, participants will complete a short questionnaire providing demographic data. Five one-to-one sessions scheduled to last up to 60 minutes will be conducted using Microsoft Teams (videoconferencing facility developed by Microsoft) video calls. After completing the eHEALS health literacy questionnaire [39], the participant will be asked to log in to DART. Using an existing or previous musculoskeletal condition to complete the assessment, they will be encouraged to give feedback using the concurrent think-aloud method [40]. This can be repeated for up to 3 different conditions. They will then complete 2 quantitative data questionnaires concerning ISO effectiveness, efficiency, satisfaction, and accessibility constructs. Satisfaction will be measured using the system usability scale. This data will inform and direct subsequent qualitative data collection. The researcher will identify variables with low scores, for example, “I found the product unnecessarily complex” and focus their qualitative questions to target these areas, interactively considering both types of data in the context of each other. The interviews will be recorded and transcribed verbatim using Otter (automated video and audio transcription software developed by otter.ai), with a final review for accuracy by the researcher using the original recording for comparison. As the study progresses and usability issues are addressed during each iteration, the emphasis for data collection moves from being largely qualitative to become more focused on the quantitative data driving the study end points. Up to 5 participants will attend a web-based session where they will be asked to explore DART. They will complete the quantitative data questionnaires and be invited to discuss any comments they may have. Qualitative questioning at this stage will be broader in nature, with postuse debrief questions as follows: (1) were you asked about what was important to you? (2) how did you find the questions? and (3) could we improve the system?

The researcher will use this opportunity to raise any previous usability problems to assess the impact of changes made to the previous iteration. The group sessions will be recorded and transcribed.

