## Discussion

### Overview of This Study

A systematic evaluation of the DART mHealth system in line with the international and national guidelines [17-20] will provide a more precise assessment of its usability and potential adoption. It will also address areas of poor usability that could otherwise become confounding factors within the subsequent noninferiority trial, where DART will be compared with current practice virtual physiotherapy triage. To date, there are no published studies evaluating similar musculoskeletal mHealth systems or indeed the knowledge of clinician error rates in usual care against which to benchmark DART. For this reason, we have set the target usability standard of 80 to be achieved, which will place DART in the top 10% of products tested using the system usability scale [41]. Usability testing will rely on an iterative convergent mixed methods design, which allows data collection specific to the functionality of the DART system, while incorporating validated and widely published usability quality measures. The iterative approach ensures that system changes made in response to identified usability problems are retested by study participants to validate the success of the updates. Based on the data collected, this section will benchmark DART usability as an app, discuss the limitations of the evaluation, and consider essential implications for future DART testing and deployment. The study methodology has been designed to rigorously test the DART mHealth app and could be adopted by other researchers to improve usability and adoption of other similar systems.

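### For problems confined to one algorithm or question path, the protocol does not secure the re-testing it says the design ensures, so end point 1 can be met with the changed path unused

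*Protocol article*

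**What the plan says.** **The tool.** Under DART Overview, "DART is a first-contact mHealth system utilizing 9 musculoskeletal clinical algorithms". On entry, "The patient selects the body region related to his/her primary problem", and the number of questions then varies with symptoms and earlier responses.

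**Closing a problem.** Under Data Analysis, the only step prescribed for Grade 1 and 2 problems is that the corrective action is done in time for the next iteration. Reassessment and possible regrading after each round are stated for Grades 3 and 4 only. Under Research Aim, Objectives, and End Points, end point 1 is reached when every Grade 1 and 2 problem has been mitigated after at least 3 user group sessions. The article does not define mitigated.

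**Re-testing.** There are two routes.
- Study Duration: "Participants who have raised high-grade usability problems will be invited to participate in a subsequent study session", so that the effect of the changes can be judged.
- Data Collection, on the group sessions: "The researcher will use this opportunity to raise any previous usability problems to assess the impact of changes made to the previous iteration".

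Group sessions hold up to 5 people, who are asked to explore the tool. No path is assigned to them.

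**The assurance.** In the Discussion (Overview of This Study): "The iterative approach ensures that system changes made in response to identified usability problems are retested by study participants".

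**The concern.** The Discussion presents re-testing by participants as a property of the design. For a fault that every user meets, such as log-in, layout or general wording, that is reasonable: any later session exercises the fix. A fault inside one body-region algorithm, or one branch of it, is different. It is re-tested only if someone takes that branch on the changed version, and neither stated route guarantees this. The raiser may decline. Raising an old problem with people who never opened that algorithm yields opinions about a change, not evidence that it works.

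End point 1 can therefore be declared met for a path-specific problem because a change was made and no one complained, when no one was in a position to complain. The end points decide when iteration stops, and the Abstract says the study is to give justified confidence for progressing to randomized trials. The Discussion also offers the protocol as a template for other developers.

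**Working it through.** **1. The plan's own yield figure.** Study Design cites 5 participants as likely to expose about 80% of usability issues. The per-user detection probability p is not given. Solving 1 − (1 − p)^5 = 0.80 gives p = 1 − 0.20^(1/5) = 0.275. A fault inside one of 9 equally used algorithms can be met by a one-region user with probability at most 1/9 = 0.111, so 5 such users reach it with probability at most 1 − (8/9)^5 = 45%. The 80% figure should not be carried over to path-specific faults.

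**2. Inputs for re-use of a changed path.**
- From the protocol: 9 algorithms; sessions of up to 5 (taken as full); at least 3 group sessions before end point 1; up to 3 conditions per person, stated for the one-to-one sessions.
- Assumed, because the protocol does not give them: equal use of the 9 regions, independent users, k different regions entered per user (k = 1, 2 or 3), and the raiser not returning.

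**3. Formula.** The chance that none of n new users enters a given algorithm is (1 − k/9)^n.

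| Regions per user | 1 session (n = 5) | 2 sessions (n = 10) | 3 sessions (n = 15) |
|---|---|---|---|
| 1 | (8/9)^5 = 55% | 31% | 17% |
| 2 | (7/9)^5 = 28% | 8% | 2% |
| 3 | (6/9)^5 = 13% | 2% | 0.2% |

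**4. Sensitivity.**
- A rarer region, entered by 5% of users: 0.95^5 = 77% in one session, 60% in two, 46% in three.
- If the raiser returns with probability a and then re-uses the path, multiply by (1 − a). With one region each, a = 0.5 gives 0.5 × 0.555 = 28% for one session and 9% for three; a = 0.8 gives 11% and 3%.
- Questions branch within a region, so re-use of the exact question path is no more likely than re-use of the algorithm.

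**5. Which column applies.** It depends on when the problem is found. One found in the interviews has all the group sessions ahead of it. One found in the last session before the additional session named in end point 2 has only that session, if the study stops at the minimum, so the one-session column applies.

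**6. Algorithms never entered at all.** With one region each and equal use, the expected number over the whole study is 9 × (8/9)^20 = 0.9 for 20 participants and 9 × (8/9)^30 = 0.3 for 30.

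**The case against.** **Re-testing does not hang on the raiser alone.** A reader might infer from Study Duration that it does. Data Collection gives a second route, open to any group participant. This stands, and it rules out the stronger claim. What remains is that this route is described as raising problems in a session, with no requirement that anyone use the path.

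**New participants are not confined to one algorithm.** A reader might infer this from "Using an existing or previous musculoskeletal condition to complete the assessment". That instruction, and the allowance of up to 3 conditions, belong to the one-to-one sessions. Group participants explore the tool, and nothing stops the researcher from directing them to a changed screen. This also stands. The 55% is therefore the least favourable case under equal use, and the 77% needs a rare region as well. But permission to direct users is not a rule that someone will be directed.

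**The affected class may be small.** Severity grading takes frequency into account, which favours widely met problems, and the article does not show how many Grade 1 or 2 problems would be path-specific. This stands.

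**An unused algorithm passing by default is not a hidden claim about the whole tool.** The limitations section says the study will not determine safety and effectiveness and concedes the small sample. Step 6 of the working suggests few algorithms would go wholly unvisited under equal use.

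**Closure rules may sit in a fuller protocol.** The article is condensed, and its design figure is not shown. Absence of a script would not be a finding. The point rests on the stated end point and the stated assurance, which the stated procedures do not support.

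**Conclusion.** The point holds for Grade 1 and 2 problems specific to one algorithm or question path. As written, end point 1 can be met though no participant used the changed path, and the Discussion's word for the assurance is stronger than the procedures allow. Problems in shared screens are not affected.

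With 9 equally used regions, full sessions of 5 independent new users and no returning raiser, the chance that a given algorithm is untouched in one session is 55%, 28% or 13% for one, two or three regions per user. Over three sessions it falls to 17% with one region each, and to 2% or less with two or three. The gap is thus largest for problems found late and for rare regions, and modest for problems found early if users explore several regions. Region shares, regions per user and acceptance of the invitation are all assumptions.

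There is also a contradiction to reconcile: the Bias section says participants will not have used DART before, while Study Duration invites raisers back.

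**What to change.** - **End point 1.** Count a path-specific Grade 1 or 2 problem as mitigated only when at least one participant has gone through the affected path on the changed version without the problem recurring at Grade 1 or 2.
- **Fallback.** If the raiser does not return, a participant already in the session does a short scripted run through that path, after completing their own assessment and the system usability scale, so that the score is not influenced.
- **Record.** Log which algorithms were exercised on which version, and limit the end-point claim to those.
- **Wording.** Restate the Discussion sentence on re-testing to match the rule adopted. Reconcile the Bias and Study Duration sections, for instance by saying that the no-prior-use condition applies at first participation.

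**Cost.** Protocol wording and a few extra minutes for one participant in sessions where a fix would otherwise go unused. The downside is that a scripted condition is less natural than the participant's own. Body region is not among the sampling characteristics ("categorizing participant characteristics of age, internet use, sex, English for Speakers of Other Languages groups"), but adding it as a quota is not advised: filling 9 regions within 20-30 people, on top of four existing characteristics, could prolong recruitment, which continues until the matrix is represented.
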